### Sample size

The sample size calculation is on the basis of the variance of outcomes. The favorable outcome of DC in previous studies ranged from 30 % to 61 % [9, 15, 41–43]. Some results may not be applicable because they included patients with diffusion injury and used DC as a secondary therapy. When primary DC treated patients for mass lesions, the favorable outcome of prophylactic DC in 781 patients was 38 % [44–54]. In our centre using therapeutic DC, the favorable outcome of therapeutic DC was 54 % [30]. After including a safety margin of 10 % to account for patients who drop out, we calculate that a sample size of 336 (each arm 168) will be sufficient to reach a significance level of 5 % (two-side) and a power of 80 %. The sample size will be re-assessed and adjusted during interim analysis.

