### Statistical analysis

The analysis will be processed on the principle of intention. Patients who drop out or violate initial distribution will be considered as the worst outcome. Considering the probability of craniotomy patients treated by salvage DC, an as-treated analysis will also be implemented, as recommended in two-arm clinic trial [39]. Parametric data will be described by mean and standard deviation. Non-parametric data will be described by median and quartile. Categorical data will be presented using number and percentage.

The primary outcome of the study will be evaluated using the Pearson chi-square test with unadjusted risk ratio and 95 % confidence interval. Adjusted analysis of primary outcome will be assessed using logistic regression for pre-specified factors and any other covariates presenting significant difference between the two groups. The pre-specified subgroups include: age, GCS, pupillary response, mass lesion type and hypotension. Secondary outcome including assessment of quality of life, mortality at 6 and 12 months and incidence of complications will also be assessed using unadjusted analysis and adjusted regression. To investigate the risk factors of postoperative refractory hypertension (salvage DC), univariate and multivariate analysis will be used to identify potential variables of craniotomy patients.

Depending on the results of regression models, the receiver operating curves will be used to evaluate the discrimination. The Hosmer–Lemeshow test will process the goodness-of-fit of models [40]. A P value < 0.05 is considered statistically significant. All statistical analysis will be computed by SPSS software (version 19.0).

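### The 10% drop-out allowance keeps 80% power only if drop-outs leave the analysis; with drop-outs scored as failures, as planned, 336 patients give about 77% at 10% equal drop-out

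*Protocol article*

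**What the plan says.** The Sample size section of the protocol article takes its control rate from pooled literature ("the favorable outcome of prophylactic DC in 781 patients was 38" per cent) and its experimental rate from the trial's own centre ("the favorable outcome of therapeutic DC was 54" per cent). It then adds a 10% allowance "to account for patients who drop out, we calculate that a sample size of 336 (each arm 168) will be sufficient" for a two-sided 5% level "and a power of 80" per cent.

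The Statistical analysis section adopts an intention-to-treat approach and fixes how losses are scored: "Patients who drop out or violate initial distribution will be considered as the worst outcome". The primary endpoint is binary (GOSE 5–8 at 12 months) and is compared by a Pearson chi-square test. A drop-out therefore enters that test as an unfavourable outcome.

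The Sample size section does not reduce the assumed rates to reflect this scoring. It does say that the sample size will be re-assessed at interim analysis.

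**The concern.** Adding patients to cover drop-out replaces people who disappear from the analysis. The number analysed returns to the required figure, and the event rates among those analysed are taken to be unchanged. Under a worst-outcome rule nobody disappears. The number analysed stays at 168 per arm, but each arm's favourable rate is scaled down, and so is the difference between the arms. The cost falls on the effect size rather than on the denominator.

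The 10% allowance was therefore set for one way of handling drop-outs and the analysis uses another. At stake is whether the 80% in the protocol is the power of the analysis that will actually be run, at the drop-out level the protocol itself allows for.

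**Working it through.** **Inputs.** Sample size section: favourable rates 0.38 and 0.54, two-sided 5%, power 80%, 168 per arm, 10% allowance. Statistical analysis section: drop-outs scored as worst outcome; Pearson chi-square test.

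**Formulas** (pooled variance, no continuity correction; p̄ is the mean of p₁ and p₂):

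- n per arm = [1.960·√(2p̄(1−p̄)) + 0.842·√(p₁(1−p₁)+p₂(1−p₂))]² / (p₁−p₂)²
- power = Φ{ [|p₁−p₂|·√n − 1.960·√(2p̄(1−p̄))] / √(p₁(1−p₁)+p₂(1−p₂)) }

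**Step 1: reproduce 336.** With 0.54 and 0.38, p̄ = 0.46, and the two square roots are 0.7048 and 0.6957. This gives n = 151.1, rounded up to 152. Then 152 × 1.1 = 167.2, rounded up to 168 per arm, or 336 in total. Dividing by 0.9 instead gives 169. The arcsine formula gives 151, and 151/0.9 rounds up to 168. The stated figure is reproduced.

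**Step 2: what the allowance assumes.** Remove 10% of 168 and about 151 per arm remain. At 54% versus 38%, power = Φ[(0.16·√151 − 1.381)/0.6957] = Φ(0.840) = 80.0%. So 80% is what 336 delivers when drop-outs are excluded.

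**Step 3: apply the stated scoring rule.** Assume 10% drop out in each arm, and that 54% and 38% are rates among patients who are followed.

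- Scored rates: 0.9 × 54% = 48.6% and 0.9 × 38% = 34.2%, a difference of 14.4 points instead of 16.
- p̄ = 0.414, and the square roots are 0.6966 and 0.6891.
- Power at 168 per arm = Φ[(0.144·√168 − 1.365)/0.6891] = Φ[(1.866 − 1.365)/0.6891] = Φ(0.727) = 76.6%.
- Exact enumeration of the Pearson test gives 77.4%.

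As a measure of the gap only, 80% at these scored rates would need n = 182.5, so 183 per arm or 366 in total, which is 30 more than 336.

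**Step 4: range under other assumptions** (168 per arm, normal approximation). The drop-out levels other than 10% are illustrative.

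| Assumption | Scored rates | Power |
|---|---|---|
| Source rates already count losses as failures | 54.0% v 38.0% | 84.0% |
| 5% drop-out in each arm | 51.3% v 36.1% | 80.5% |
| 8% in each arm | 49.7% v 35.0% | 78.2% |
| 10% in each arm | 48.6% v 34.2% | 76.6% |
| 12% therapeutic, 8% prophylactic | 47.5% v 35.0% | 64.9% |
| 8% therapeutic, 12% prophylactic | 49.7% v 33.4% | 85.9% |

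In the last two rows the imbalance changes the scored difference between the arms. The higher figure reflects a difference inflated by the scoring and is not a real gain.

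**The case against.** The strongest reply is that 77% is conditional. The article does not say whether the studies behind 38% and 54% counted losses as failures. If they did, there is no further dilution and 336 gives 84.0%. There is also an intermediate case: if the two rates describe all randomised patients, and the 10% who drop out would have done well half as often as average, the scored rates are 51.3% and 36.1% and power is 80.5%. The fallback routes in the follow-up section (posted questionnaire, then a surrogate by telephone) may keep losses below 10%. The allowance can also be read as a cushion rather than a forecast. All of this stands, and it is why the result has to be given with its assumptions and a range. It does not restore the stated derivation: the assumption under which the 10% inflation yields 80% is that the rates apply to followed patients, and the article argues no other.

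Two other provisions might seem to settle the matter. Interim re-assessment could change the sample size later, but it does not correct the power now stated for 336. The provision that surrogates of patients who exit early decide whether earlier data may be used could be read as removing some patients altogether. The analysis section nevertheless scores drop-outs as worst outcome.

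A reader might infer that the allowance and the scoring rule are incompatible. That goes too far: the extra patients absorb part of the dilution, and power is still 80.5% at 5% drop-out. A reader might also put a lower figure on power because allocation violators are scored as failures too. A further 5% of violators, for example, would give 72.6%. The direction is right if violations are similar in both arms, but the article gives no violation rate, so no such figure belongs in the text.

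**Conclusion.** The point holds in a limited form. At the protocol's own 10% allowance, its own analysis rule gives about 77% power at 336 rather than 80%, a shortfall of about 3 points. This assumes equal drop-out in the two arms and that 38% and 54% are rates among followed patients. Other assumptions move the figure in both directions, from 64.9% to 85.9% across the cases examined. Allocation violators would lower it further by an amount that cannot be stated from the article.

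The document does not support a claim that the trial is seriously underpowered, or that the sample size must rise. What is wrong as written is the stated power, because it belongs to an analysis that excludes drop-outs.

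**What to change.** In the Sample size section, restate the power as about 77% at 336 (168 per arm), given 10% drop-out in each arm scored as worst outcome and 38% and 54% taken as rates among followed patients. Add the range: 80.5% at 5% drop-out, 84.0% if the source rates already count losses as failures, and 64.9% to 85.9% for a 12%/8% imbalance. Say that allocation violators scored as failures are not covered by the allowance.

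The cost is a sentence or two and a slightly less favourable stated power. No extra patients are needed. Replacing worst-outcome scoring with imputation would also bring the allowance and the 80% into line, but it changes the primary analysis and is a debatable trade-off; this point does not require it.

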### Randomization

Computer-based central randomization will allocate treatment with minimizing following covariates: age (<40 or ≥ 40 years), GCS (8-6 or 5-3), pupillary response (both reactive or one reactive or no reactive), mass lesion type (subdural or intracerebral) and hypotension. A random element will be introduced to enhance the unpredictability of the minimization algorithm [55]. Physicians can use telephone or computer to register and randomize eligible patients. The patients will be assigned to either the therapeutic DC group or the prophylactic DC group and will receive a unique identity number for PRECIS records.

### Blinding

Since the study is conducted at a single center and interventions probably result in different outcomes and qualities of life, ‘ideal blinding’ is not realistic in PRECIS. We use an assessor-blinding method to investigate the study outcome. The independent assessors (IAs) will not be involved in the randomization or intervention. IAs will not be able to obtain the distribution information or the specific treatment procedures using CRF.

### Quality control and trial administration

#### Data safety monitoring board

The independent data safety monitoring board (DSMB) is established to ensure patient safety and data confidentiality. The members of DSMB include neurosurgeons, neurology physicians, ethicists and biological statisticians. The board members should have no conflicts of interests concerning the trial. DSMB is granted the highest authority to access the database. DSMB will launch interim analyses and further to recommend to the study group. The closed part of the interim analysis will be confidential to TMT and related staff. The recommendations will only suggest terminating the trial if one branch is significantly different (i.e. >3 SDs) with respect to primary endpoints or SAEs

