## Background

Severe traumatic brain injury (STBI) is a major cause of death in young adults in developed countries [1]. In China, due to increasing traffic accidents, head injury occurs above 1 per 1000 [2]. The mortality of STBI is between 30 % and 50 %. According to a report from the Asian Development Bank, the annual economic loss from traffic accidents is equivalent to 1 %–3 % of China’s gross national product [3]. Considering the per capita income and limited medical resources, rational and effective treatment of STBI is of important economic and social significance.

Most STBI patients with intracranial hypertension attribute to mass lesions, such as contusion and subdural haematoma (SDH) [4, 5]. Severe primary injury and exasperate condition necessitate emergent surgical intervention. The available type of operation is either craniotomy or decompressive craniectomy (DC).

Craniotomy is the most widely used surgical treatment for STBI. This operation keeps the skull intact but the risk of post-operative refractory hypertension remains; thus, requires a salvage surgery. DC is another broadly used operation for STBI rescue, which involves the removal of the frontal, parietal and temporal skull to expand fixed cranial cavity. Some studies indicated that DC could effectively alleviate refractory intracranial hypertension [6–10]. However, using DC to treat STBI has been controversial since the 1970s [11, 12]. The focus of debate resides in whether DC would be able to improve the prognosis of patients. Current guidelines only suggest performing set the role of DC as a ‘surgical choice’ [5, 13].

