### Outcomes

The Primary endpoint is a favorable outcome at 12 months after randomization as measured by GOSE (5–8). The core secondary endpoint is the quality of life indicated by EQ-5D. Further secondary endpoints include mortality and complications at corresponding time point, ICP and CPP control and incidence of salvage DC in craniotomy patients.

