### Adverse events (AEs) and Serious adverse events (SAEs)

Both AEs and SAEs will be recorded in CRF. AE is defined as any unintended or unfavorable disease that occurs during the study. AEs include DC related complications, such as cortical herniation, hemorrhage evolution, infection, hydrocephalus and subdural hygroma. SAEs are defined as any of the following: death, life-threatening events, persistent vegetative state, requirement of hospitalization and prolonged hospitalization. Once the attending physicians realize SAE, it should be reported to the trial management team (TMT) and BMEC within 24 h. SAEs will be followed up until the issue is properly resolved.

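### Harm and benefit share one exclusive 3 SD bar for a DSMB recommendation to terminate, and deaths are not named as a comparison of their own

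*Protocol article*

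**What the plan says.** The section on the data safety monitoring board has the DSMB launch interim analyses and make recommendations. It then limits one kind of recommendation: "The recommendations will only suggest terminating the trial if one branch is significantly different (i.e. >3 SDs) with respect to primary endpoints or SAEs". No direction is given, and the number and timing of looks are not stated.

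Death reaches this rule by two routes:

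- **As an SAE.** The adverse events section states: "SAEs are defined as any of the following: death, life-threatening events, persistent vegetative state, requirement of hospitalization and prolonged hospitalization". Death is one of five listed types.
- **As an unfavourable outcome.** Under Outcomes: "The Primary endpoint is a favorable outcome at 12 months after randomization as measured by GOSE (5–8"). A patient who has died cannot score 5 to 8.

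Mortality itself is placed lower: "Further secondary endpoints include mortality and complications at corresponding time point". The stopping guideline does not name it. For scale, the Background states: "The mortality of STBI is between 30 % and 50" %.

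The steering team takes final decisions following DSMB recommendations, and the management team's duties include patient safety. Neither section adds a separate rule for harm.

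**The concern.** A 3 SD bar (two-sided p = 0.0027) is a familiar way to keep early looks from spending much of the type I error on a claim of benefit. That reason does not carry over to an excess of deaths, where the question is whether it remains acceptable to randomise. Here the same bar governs both directions, and 'only' makes it exclusive. Read literally, a DSMB that saw a 2.5 SD excess of deaths could not recommend termination.

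Both named triggers also mix death with other events. The SAE list sets it beside vegetative state and hospitalization, and the dichotomised GOSE sets it beside severe disability. In a population where the article expects 30 % to 50 % to die, a moderate but real mortality difference could persist through the interim looks without meeting the guideline.

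**Working it through.** **1. The plan's own figure.** The Sample size section gives "the favorable outcome of prophylactic DC in 781 patients was 38" % and "the favorable outcome of therapeutic DC was 54" %, with two-sided 5 %, 80 % power and 10 % for dropout. The usual formula is

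`n = [1.96·sqrt(2·p̄(1−p̄)) + 0.842·sqrt(p1(1−p1)+p2(1−p2))]² / (p2−p1)²`

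With p1 = 0.38, p2 = 0.54 and p̄ = 0.46, n = 151.1, so 152 per arm. Then 152 × 1.10 = 167.2, so 168 per arm and 336 in total. The stated size reproduces and is not at issue.

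**2. Assumptions.** '3 SDs' is read as |z| > 3 for the difference between two proportions. The article gives no interim timing, so I take a single look at half accrual (84 per arm), and separately three looks at 42, 84 and 126 per arm. Arm-specific mortality is not given. I assume 30 % in one arm and a higher rate in the other. Rates of 40 %, 45 % and 50 % lie within the Background range; 55 % lies beyond it and is included to show the limit.

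**3. Deaths compared alone, one look.** For 30 % v 45 % at 84 per arm:

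`z = 0.15 / sqrt((0.30·0.70 + 0.45·0.55)/84) = 0.15/0.0738 = 2.03`

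P(z > 3) = 1 − Φ(3 − 2.03) = 0.167 and P(z > 2) = 1 − Φ(2 − 2.03) = 0.513. Binomial simulation with a pooled standard error (400,000 runs) gives 0.160 and 0.511.

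The smallest observed excess that crosses at 84 per arm, starting from 25 deaths, is 25 v 45 (z = 3.13); 25 v 44 gives z = 2.98. That is 20/84, about 24 points.

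**4. Chance of crossing 3 SDs in the harm direction, deaths alone (simulation).**

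| True mortality | One look, 84 per arm | Any of three looks (42, 84, 126) |
|---|---|---|
| 30 % v 40 % | 5 % | 11 % |
| 30 % v 45 % | 16 % | 33 % |
| 30 % v 50 % | 36 % | 63 % |
| 30 % v 55 % | 61 % | 87 % |

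**5. If deaths were pooled into one any-SAE proportion.** The article does not prescribe this. With death rate d and a share q of survivors having another SAE, the rate is d + (1 − d)q, so a 15-point gap in deaths shrinks to 0.15(1 − q). At 84 per arm and 30 % v 45 % deaths, q = 0.3, 0.5 and 0.8 (assumed) give z = 1.38, 1.05 and 0.59. The chances of crossing are about 5 %, 2.6 % and 0.8 %. The direction is clear, but the size depends on a rate the article does not state.

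**6. Cost of a lower review threshold.** With equal mortality of 30 %, a two-sided 2 SD threshold is crossed in about 5 % of trials at each look and in about 10 % over the three looks.

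**The case against.** A reader might infer stronger things that the text does not support.

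- **That deaths are pooled with other SAEs.** The adverse events section defines which events count; the DSMB section does not say how arms are compared. Comparing deaths, a listed SAE type, on their own fits the wording equally well. The pooled figures are only a what-if.
- **That any large excess would usually be missed.** This fails for larger gaps. With several looks, which the plural 'interim analyses' suggests, 20- and 25-point excesses cross more often than not.
- **That a death stays invisible to the primary endpoint until month 12.** A death is a known failure on GOSE 5–8 when it occurs. What remains true is that the dichotomy mixes death with severe disability.
- **That the trial would necessarily go on recruiting.** 'Only' restricts recommendations to terminate. It does not bar review or other advice below 3 SDs. SAEs, including deaths, go to the management team and the ethics committee within 24 hours.

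It can also be said that a symmetric 3 SD guideline is a legitimate choice, and that harm guidance usually sits in a charter or full protocol not shown here. Silence on mortality-specific guidance would indeed be no finding. But the article does not stay silent: it states an exclusive rule, and a charter permitting termination for harm below 3 SDs would contradict it. Finally, setting a 3 SD termination bar beside a 2 SD review bar is not like for like. The 51 % in step 3 shows how often a review would be prompted, not how often the trial would stop.

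**Conclusion.** The point holds as a defect in a stated rule: one undirected and exclusive bar governs both benefit and harm, and all-cause death is not named as its own comparison. Its practical weight is greatest for moderate excesses. A true 15-point difference in mortality, with deaths compared alone, would meet the guideline in roughly one trial in six at half accrual and one in three over three looks. For differences of 20 points or more the guideline is met in most trials over three looks. These figures rest on assumed interim timing, an assumed 30 % mortality in the better arm, and reading '3 SDs' as a z statistic. Pooling with other SAEs would lower them by an amount that cannot be fixed from the article. The wording should be changed; the sample size and the 3 SD guideline for benefit are not in question.

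**What to change.** In the data safety monitoring board section:

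1. Keep more than 3 SDs on the primary endpoint as the guideline for recommending a stop for benefit.
2. Remove 'only' as it applies to harm, so that the DSMB may use its judgement below that bar.
3. State that all-cause deaths by arm are compared on their own at each interim analysis against a less stringent threshold set by the DSMB. Crossing it prompts a DSMB review and does not stop the trial automatically.

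The value of that threshold is the DSMB's choice. Two SDs is used above for illustration only.

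The cost is wording in the protocol and any DSMB charter. Deaths are already recorded and the committee already exists, so no further patients or data are needed. The downside is some unneeded reviews under equal mortality, at the rates in step 6 if 2 SDs were chosen. Power could also fall a little if a review led to a stop; that loss has not been quantified.

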#### Trial steering team

The trial steering team is responsible for supervising the overall process of the trial and final decisions following recommendations from DSMB.

#### Trial management team

The responsibilities of TMT include trial conception, intervention design, patient safety, quality assurance, data analysis and writing. TMT will periodically instruct each team to conduct coordination meetings. According to recommendations from the interim analysis, TMT will re-calculate and adjust the sample size if needed.

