#### Trial assistant team

The assistant team is composed of IAs and computer support group (CSG). Following the principle of blinding, IAs will complete study outcome assessment and submit to DSMB (owning priority) and TMT. CSG will perform the online random allocation system, database establishment and maintenance.

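### The management team receives outcomes and recalculates the sample size after the interim analysis; nothing stated keeps this blind to the arm comparison, and the final test stays at 0.05

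*Protocol article*

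**What the plan says.** Five places in the protocol article bear on this.

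- **Sample size:** the target is 336 patients, 168 per arm, and "The sample size will be re-assessed and adjusted during interim analysis".
- **Trial management team:** "According to recommendations from the interim analysis, TMT will re-calculate and adjust the sample size if needed". On its wider role: "The responsibilities of TMT include trial conception, intervention design, patient safety, quality assurance, data analysis and writing".
- **Trial assistant team:** "IAs will complete study outcome assessment and submit to DSMB (owning priority) and TMT". The DSMB has precedence, but TMT is also a recipient, and no hold until lock is stated.
- **Data safety monitoring board and Trial steering team:** "DSMB will launch interim analyses and further to recommend to the study group". A stop is suggested only for a difference between arms beyond 3 SDs on the primary endpoint or serious adverse events. On access: "The closed part of the interim analysis will be confidential to TMT and related staff". The steering team takes "final decisions following recommendations from DSMB".
- **Statistical analysis:** the primary endpoint is tested by a Pearson chi-square test, with significance at P below 0.05. No adjustment for a changed sample size is mentioned.

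**The concern.** A closed interim report exists so that those running the trial do not learn how the arms compare while patients are being recruited. Here the team that designed the intervention, and will analyse the data, also receives outcome assessments and resets the sample size. The trial is single-centre, and the Blinding section accepts that full blinding is not realistic. A team with these duties could plausibly link outcomes to arms.

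Two things are at stake. The first is the 5% level. If the new sample size depends on the observed difference, the weight of the second-stage data depends on the first-stage result, and the ordinary chi-square statistic no longer has its nominal null distribution. The second is confidentiality. A sample size derived from the observed effect lets a reader who knows the rule work back to that effect.

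**Working it through.** **1. The stated roles side by side**

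| Step | Who | Section |
|---|---|---|
| Runs interim analyses, recommends | DSMB | Data safety monitoring board |
| Final decision on recommendations | Steering team | Trial steering team |
| Recalculates and adjusts N | TMT | Trial management team |
| Receives outcome assessments | DSMB first, and TMT | Trial assistant team |
| Relation to the closed results | TMT, ambiguous | Data safety monitoring board |

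The access sentence can mean withheld from TMT or restricted to TMT. If withheld, the outcome route and the recalculation duty sit badly with it. If restricted to TMT, the team sees the comparison outright. Either way the sections need reconciling. The basis of the recalculation (pooled rate or between-arm difference) is stated nowhere.

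**2. The planned size reproduces**

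Inputs from the Sample size section: 38% and 54% favourable, two-sided 5%, 80% power, 10% drop-out.

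n per arm = [1.96·√(2·0.46·0.54) + 0.84·√(0.38·0.62 + 0.54·0.46)]² / 0.16² = 151.1, so 152. Then 152 × 1.10 = 167.2, so 168; 152 / 0.90 = 168.9, so 169. The stated 168 is confirmed.

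**3. Type I error if the observed effect sets N**

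The protocol gives no rule, so these are assumptions: one look at 84 per arm (half of 168), a stop if |z1| > 3, otherwise N reset to 80% power at the observed effect.

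N per arm = 84 × (2.8 / |z1|)², clipped to the limits. For example, z1 = 1.5 gives 84 × 3.484 = 293 per arm, 1.74 times the plan.

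Final z = [√84·z1 + √(N − 84)·z2] / √N, with z2 an independent standard normal value; reject if |z1| > 3 or |final z| > 1.96. Simulation under no effect (millions of trials per scenario):

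| Cap on N | Increases only | N may also fall |
|---|---|---|
| 1.5 × | 5.7% | 6.4% |
| 2 × | 6.1% | 6.8% |
| 3 × | 6.5% | 7.2% |

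A binomial simulation with 76 evaluable per arm at the look, no 3-SD stop and caps of 2 to 3 times gives 5.8% to 6.5% with increases only, and 6.8% to 7.4% if N may fall.

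**4. Other rules, final test still at 0.05**

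| Rule | Two-sided type I error |
|---|---|
| 80% conditional power at the observed trend, looks at 25% to 75%, caps 1.5 to 3 ×, 3-SD stop: increases only | 5.6% to 7.1% |
| Same, N may fall | 6.9% to 8.3% |
| Pooled-rate re-estimation at half the evaluable patients, null rates 38% to 54% | 4.9% to 5.1% |
| Fixed 152 per arm, same null rates (benchmark) | 4.8% to 5.1% |
| 3-SD look alone, at 25% to 75% | 5.0% to 5.2% |

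The excess therefore comes from using the between-arm result to set N. Neither the 3-SD look nor re-estimation as such produces it.

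**5. Does the design imply an effect-based rule?**

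With the 16-point difference fixed, the pooled rate has almost no room to raise N: 151.1 per arm at a pooled 46%, and at most 152.1 at 50%. That might suggest that any material increase must come from the observed effect. But if the planned ratio 0.54/0.38 were held instead, a pooled rate of 40% would need about 193 per arm and 36% about 229. Drop-out of 20% gives 152 / 0.80 = 190, and 30% gives 152 / 0.70 = 217. N can therefore rise materially without any arm comparison, and this argument does not settle which rule is meant.

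**The case against.** The strongest reply is that the text nowhere says the observed effect is used. A pooled-rate recalculation would leave the level at about 5%. A condensed article may properly leave the rule, timing, cap and any alpha adjustment to an analysis plan or DSMB charter. This stands: the absence of those details is not the point here, and a reader who infers that the type I error does exceed 5% goes beyond the documents.

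On confidentiality, a reader might infer that TMT sees the accumulating comparison. The documents do not support that. The Blinding section denies the assessors access to allocation, so nothing shows that their submissions carry arm labels. The allocation system is run by the computer support group. TMT acts on recommendations, and its data-analysis duty may refer to the final analysis only. Nor does TMT plainly act alone, because the steering team has the final decision on DSMB recommendations.

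What the reply does not remove is the stated arrangement. The outcome route to TMT and the assignment of the recalculation to TMT are written rules. Nothing stated restricts them to blinded data, and they conflict with a closed interim report if that report is meant to be closed to TMT. If comparative data were used, the stated test would not hold its level.

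**Conclusion.** The point holds as a conditional risk. The protocol has a team that receives outcomes recalculate the sample size after an interim analysis, states no limit to blinded data, and keeps an ordinary test at 0.05. With an effect-based recalculation, type I error would be about 5.7% to 7.2% under the assumed one-look rule and about 5.6% to 8.3% under conditional-power rules. With a pooled-rate recalculation it would be about 4.9% to 5.1%. Look time, reset rule and caps are assumptions, because the protocol gives none. Interim confidentiality is unprotected, but no breach is shown. The change should be made before the first interim look.

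**What to change.** - State that re-estimation uses only the pooled (blinded) favourable-outcome and drop-out rates, with the 16-point difference held fixed and increases only. The DSMB statistician does it and tells TMT only the new N.
- Have the assessors submit outcomes only to the central database and the DSMB until lock.
- Reword the sentence on the closed part to say who is denied those results, and reconcile it with the sections on the steering, management and assistant teams.
- If effect-based re-estimation is wanted, pre-specify a fixed-weight combination test for the primary endpoint.

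The cost is protocol and charter wording and changed access rights, with no added patients or staff. TMT loses early sight of outcomes. Its safety role need not suffer, because the adverse-events section already sends it serious adverse events within 24 hours; for the same reason it will still learn of deaths and persistent vegetative state. With the 16-point difference fixed, the pooled rate can add only about one patient per arm, so in practice drop-out is what would raise N.
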